**Figure 2 F2:**
[figure not shown]
Protocol pipeline. AUC, area under the curve; AUPRC, area under the precision-recall curve; Cox PH, Cox proportional hazards; CV, cross-validation; ML, machine learning; PWH, people with HIV; SHAP, SHapley Additive exPlanations.

#### Substudy—PWH only

An analysis will be conducted with PWH only. A simple Cox PH regression model will be developed using preselected covariates using existing knowledge of risk factors. An exploratory approach will be followed, implementing ML methods to handle overfitting and class imbalance as needed. The prediction performance will be assessed using the same methods as the previous models and compared.

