#### Data preparation

For this study, we will use complete cases only since missing data are minimal. Variables missing more than 10% of the data will be omitted, and after that, any observations with missing data will be dropped.^32^ For the ML analyses, the data will be split 80% into training and 20% into test sets based on follow-up time. The variables in each set will be further prepared to optimise their analysis. Categorical variables will be transformed using one-hot encoding. Normalisation and standardisation of variables will be applied where necessary.

The participants will be matched 1:10 using the entire HIV-negative population in Sweden that fit the criteria. They will be matched on age, legal sex, region of birth and comorbidities including hypertension, chronic obstructive pulmonary disease, diabetes and previous cancer diagnosis.^33
34^ The standardised mean difference of the cohorts will be compared from before and after matching to confirm consistency. Power was calculated using the full anticipated study population consisting of just over 13 000 PWH matched 1:10 to approximately 130 000 PWoH. Median follow-up time is estimated to be at least 10 years in both groups. The expected incidence rate of CRC used for the calculation was the Swedish age-standardised incidence rate reported by the European Commission (129.1 per 100 000 population).^35^ Based on these assumptions and using a two-sided alpha of 0.05, the study is estimated to have 80% power to detect an HR of approximately 1.20 or greater.

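### The PWH-only models appear to be evaluated on one 20% hold-out with roughly 34 CRC events, too few to detect modest differences between models; resampling over all PWH should be added

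*Protocol article*

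**What the plan says.** Under Data preparation the protocol article fixes one partition: "For the ML analyses, the data will be split 80% into training and 20% into test sets based on follow-up time". The section on unsupervised ML uses Time Series Split cross-validation for training and meta-learning. The section on stacking then generates the final risk scores on the test set and gives balanced accuracy the most weight among the performance measures.

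The substudy section says "An analysis will be conducted with PWH only" and that "The prediction performance will be assessed using the same methods as the previous models and compared". It describes the approach as exploratory and does not restate the split. The sensitivity analysis on incomplete data, also in PWH only, is to be compared with the substudy results.

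The only size justification is under Data preparation: "Power was calculated using the full anticipated study population", that is "just over 13 000 PWH matched 1:10 to approximately 130 000 PWoH". It concerns an HR. No expected event count is given for PWH or for any test set.

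**The concern.** The stated aim is a risk prediction model for PWH, and the substudy is the analysis restricted to that population. Its purpose is comparative: a simple Cox model against ML methods, PWH-only models against the pooled ones and, through the sensitivity analysis, complete-case against incomplete-data handling. How well these comparisons can be made depends mainly on the number of CRC events among PWH in the evaluation data. If only a fifth of those events is used, a real but modest advantage of one approach may go unseen, and a chance difference may be read as an advantage. The introduction reports that earlier comparisons of ML with regression reached differing conclusions, so modest differences are a realistic expectation.

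**Working it through.** **Inputs from the protocol article (Data preparation).** 13 000 PWH and 130 000 PWoH; follow-up: "Median follow-up time is estimated to be at least 10 years in both groups"; CRC rate 129.1 per 100 000, read as per person-year; test share 20%; power statement: "using a two-sided alpha of 0.05, the study is estimated to have 80% power to detect an HR of approximately 1.20 or greater".

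**Inputs assumed here.** Sensitivity and specificity 0.70; c-statistic 0.75; correlation ρ between two models scored on the same people, 0.5 to 0.9; test set holds 20% of people and 20% of events.

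**1. The protocol's own power figure.** At 10 years and HR 1.20:
- PWH events: 13 000 × 10 × 0.001291 × 1.20 = 201.
- PWoH events: 130 000 × 10 × 0.001291 = 1 678.
- Total: about 1 880.

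Schoenfeld with allocation 1/11: √(1 880 × 10/121) × ln 1.20 − 1.96 = 0.31, so power is 62%. Power of 80% needs 2 858 events, which is about 15.2 years. The stated 80% is therefore not reproduced at exactly 10 years but is reproduced at about 15, and the wording of the follow-up assumption allows that. This serves here only to set an upper follow-up scenario.

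**2. PWH events in total and in the test set.**

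| Scenario | PWH events | 20% in test set |
|---|---|---|
| 10 years, HR 1 | 13 000 × 10 × 0.001291 = 168 | 34 |
| 10 years, HR 1.20 | 201 | 40 |
| 15.2 years, HR 1 | 255 | 51 |
| 15.2 years, HR 1.20 | 306 | 61 |

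**3. Precision for one model, 34 events and 2 566 non-events.**
- Sensitivity: SE = √(0.7 × 0.3/34) = 0.079; half-width 15.4 points.
- Balanced accuracy: SE = 0.5 × √(0.21/34 + 0.21/2 566) = 0.0396; half-width 7.8 points.
- c-statistic 0.75 (Hanley-McNeil): SE = 0.0488; half-width 0.096.

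**4. Precision for the difference between two models.** SE of the difference = SE × √(2(1 − ρ)), for balanced accuracy. Power is for a 5-point difference, two-sided 0.05.

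| Events evaluated | ρ = 0.5 | ρ = 0.7 | ρ = 0.8 | ρ = 0.9 |
|---|---|---|---|---|
| 34 | 24% | 37% | 52% | 81% |
| 61 | 39% | 59% | 76% | 97% |
| 168 (all PWH) | 80% | 95% | 99% | 100% |

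At ρ = 0.7 the difference detectable with 80% power is 8.6 points with 34 events, 6.4 points with 61 and 3.9 points with 168.

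**5. Effect of evaluating on all PWH (168 events).** The half-width falls from 7.8 to 3.5 points for balanced accuracy and from 0.096 to 0.043 for a c-statistic of 0.75 (0.099 to 0.045 at 0.70). This treats out-of-fold predictions as independent, so the gain is somewhat optimistic.

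**The case against.** **The single hold-out in the substudy is inferred.** The sentence about using the same methods could refer only to the performance measures, and Data preparation ties the split to the ML analyses. This stands as a caveat. The hold-out remains the natural reading, because the article describes no other way of obtaining final performance.

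**34 is not a ceiling.** A reader might infer that the test set holds at most 34 events. The documents do not support that: 10 years is a lower bound and the figure assumes HR 1. Nor is 34 a floor. The rate used is the "Swedish age-standardised incidence rate reported by the European Commission (129.1 per 100 000 population"), which need not be the rate in PWH; incomplete cases are dropped; and a split by follow-up time need not place 20% of events in the test set. The article quantifies none of these.

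**Single-model intervals do not measure a comparison.** Correct: models scored on the same people are correlated, which is why step 4 works with paired differences. A reader might infer that the PWH comparisons would be settled by noise. That goes too far. At ρ = 0.7 a difference of about 9 points would be seen, and at ρ = 0.9 even 5 points has 81% power.

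**A time-based hold-out has its own value.** It tests later-period performance, which random resampling does not. This stands, and it is a reason to keep the hold-out rather than replace it.

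**The stakes are limited.** The substudy is exploratory, and the article requires external validation and prospective evaluation before clinical use. This lowers the urgency, but the comparisons are still planned.

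**Conclusion.** The point holds in a limited form. On the natural reading, the PWH-only models are compared on one test set with about 34 CRC events (roughly 34 to 61 on the protocol's inputs, possibly fewer). With 34 events, a 5-point paired difference in balanced accuracy has 24% to 52% power at correlations of 0.5 to 0.8, so modest differences cannot be detected reliably, while large ones or those between very highly correlated models can. Allowing 61 events softens this but does not remove it. The result rests on a 20% event share, sensitivity and specificity of 0.70, and assumed correlations; the protocol gives none of these for the substudy.

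A reader might also infer from step 1 that the stated power is wrong. That does not follow, because follow-up is given as a minimum. Nor is the time-based split an error in itself. The weakness is that it appears to be the only evaluation of the PWH-only models. This is a recommended improvement, not a fault that invalidates the study.

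**What to change.** For the PWH-only substudy and the incomplete-data sensitivity analysis:

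- Add repeated nested cross-validation or bootstrap optimism correction over all PWH. Repeat every modelling step (scaling, clustering or dimension reduction, tuning and, where used, stacking) inside each resample.
- Base the model comparisons on paired differences with 95% CIs.
- State the expected number of PWH events, in total and in the test set, and say explicitly how the substudy models are validated.
- Keep the time-based hold-out and report it alongside as the later-period check.

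This needs more computing time and about a paragraph of text, with no new data. The drawback is that the resampled estimate is internal validation, and its gain in precision will be somewhat smaller than calculated above because out-of-fold predictions are not independent.

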This study will use comprehensive nationwide data and apply machine learning (ML) methods to develop a CRC risk prediction model. PWoH will be included to increase statistical power. Matching will be used to control for key confounders, and appropriate methods will be applied to minimise bias and prevent overfitting during model development. Sensitivity and subgroup analyses will be conducted to compare model performance across different scenarios. ML-based prediction models may be superior to logistic or Cox proportional hazards (PH) regression-based models. Previous research studies have compared these approaches, resulting in varying conclusions. Some ML methods have been observed to perform as good as, or may be favourable to, Cox PH or logistic regression for some prediction tasks.^8–12^ Logistic or Cox PH regression methods may perform prediction tasks better or worse than some ML approaches,^11^ but data-driven approaches using ML have been favoured in some studies due to their ability to understand complex relationships in data, which may have an advantageous prediction performance.^12^ It may be more difficult to motivate an ML approach in a resource- or time-limited setting, in particular if data quality or dimensionality is lower and Cox PH or logistic regression methods can complete prediction tasks to a comparable level.

This protocol will use an ensemble method called stacking,^13^ which will combine the predictions of multiple ML models to produce an overall predicted risk score of CRC. Each ML method relies on different statistical assumptions and processes that may reflect different patterns in the data and offer unique insights into the relationships between variables and the outcome.^14^ By leveraging the estimates from each model in the ensemble, the perspectives from diverse model approaches can be integrated to create a more robust and accurate prediction.^15–17^ The performance of the ensemble model approach will be compared with the performance of a Cox PH regression model.

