#### Stacking and dissemination

Stacking, an ensemble learning method, will be used to combine predictions from the previously described ML models.^43^ The base learners will generate out-of-fold risk scores using Time Series Split, which will then serve as inputs to a Cox-PH model as the meta-learner. Finally, the trained base learners and meta-learner will then be used to generate final risk score predictions on the test set.

The performance of the stacked models will be primarily evaluated using balanced accuracy,^44^ and additionally assessed with the concordance index,^45^ Brier score,^46^ time-dependent area under the curve and area under the precision-recall curve (AUPRC), before variable importance is assessed.^13
47
48^ All metrics will be thoroughly considered, but the balanced accuracy of each prediction performance will be weighted most due to its handling of class imbalance, considering both sensitivity and specificity.^44^ AUPRC is preferred over area under the receiver operating curve due to its ability to better handle class imbalance, which will be a factor in this study.^49^

The model reporting will adhere to the TRIPOD+AI statement.^50^ The variable importance results will additionally be considered separately. A summary of the analysis plan is illustrated in figure 2.

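### The comparison of PWH-only models with the main models is not tied to a common set of held-out PWH, so the two sets of performance figures are not comparable

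*Protocol article*

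**What the plan says.** All places are in the Protocol article.

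- **Data preparation.** The main data set is "just over 13 000 PWH matched 1:10 to approximately 130 000 PWoH", and "the data will be split 80% into training and 20% into test sets based on follow-up time". No restriction of the test set to PWH is stated.
- **Stacking and dissemination.** The trained learners are "used to generate final risk score predictions on the test set". "The performance of the stacked models will be primarily evaluated using balanced accuracy", with the concordance index, Brier score, time-dependent AUC and AUPRC alongside. Of the last it says "AUPRC is preferred over area under the receiver operating curve due to its ability to better handle class imbalance".
- **Substudy—PWH only.** "An analysis will be conducted with PWH only": a simple Cox model with preselected covariates, then exploratory ML as needed. "The prediction performance will be assessed using the same methods as the previous models and compared".
- **Introduction.** The stated reason for the HIV-negative group is "PWoH will be included to increase statistical power". The section also promises sensitivity and subgroup analyses in general terms.
- **Study aims.** The models are intended for PWH, with PWoH as additional data.

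**The concern.** The substudy commits to setting PWH-only performance beside the performance of the earlier models. The text does not say that the earlier models will be scored on held-out PWH, or that the two analyses will share test individuals. If each is scored on its own test set, the difference between the figures mixes three things: the models, the people they were scored on and, for AUPRC and Brier, the event rate.

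Two things are at stake. First, this is the only planned analysis that puts models built with and without PWoH side by side, so readers will use it to judge whether adding PWoH helped. Second, a pooled score made up mostly of PWoH says little about how the model performs in the patients for whom it is meant.

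**Working it through.** The plan gives no performance figure to reproduce. Its power paragraph (Data preparation) supplies the inputs: 13 000 PWH, 130 000 PWoH, a CRC rate of 129.1 per 100 000 (taken as per person-year), follow-up of 10 years (the stated minimum for the median) and HR 1.20. My assumptions are an AUC of 0.75 (0.70 and 0.80 for range), HRs of 1.0, 1.5 and 2.0 for range, 10-year risk = rate × 10, and a 20% test set with the 1:10 ratio preserved.

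**1. Who is in each test set**

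- PWH: 0.2 × 13 000 = 2 600. PWoH: 0.2 × 130 000 = 26 000. PWoH share: 26 000 / 28 600 = 10/11 = 90.9%.
- Risk in PWoH: 0.001291 × 10 = 1.291%. Events: 26 000 × 0.01291 = 336.
- Events in PWH: 2 600 × 0.01291 = 34 at HR 1.0, and × 1.2 = 40 at HR 1.20.
- Share of pooled test events in PWoH at HR 1.20: 336 / 376 = 89%.

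**2. Prevalence effect at equal discrimination**

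Scores are N(0,1) in non-cases and N(d,1) in cases, with d = √2·Φ⁻¹(0.75) = 0.954, the same in PWH and PWoH. Each model is calibrated to its own population. With prevalence π and S the upper-tail normal probability:

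- Pooled prevalence: π = (HR × 1.291% + 10 × 1.291%) / 11. The PWH are part of the pooled set, so this rises with HR.
- Precision at t: πS(t−d) / [πS(t−d) + (1−π)S(t)]. AUPRC is its average over the cases.
- Brier: the mean of q(1−q), where q is the true posterior risk at each score.
- Balanced accuracy at the cut-off d/2: Φ(d/2) = Φ(0.477) = 0.683, with no π in it.

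| HR | Prevalence, pooled / PWH | AUPRC, pooled / PWH | Change | Brier, pooled / PWH | Change |
|---|---|---|---|---|---|
| 1.0 | 1.29% / 1.29% | 0.049 / 0.049 | 0 | 0.0125 / 0.0125 | 0 |
| 1.2 | 1.31% / 1.55% | 0.050 / 0.058 | +16% | 0.0127 / 0.0149 | +17% |
| 1.5 | 1.35% / 1.94% | 0.051 / 0.071 | +39% | 0.0131 / 0.0185 | +42% |
| 2.0 | 1.41% / 2.58% | 0.053 / 0.092 | +73% | 0.0136 / 0.0243 | +79% |

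Balanced accuracy (0.683) and AUC (0.750) are the same in every row. For AUCs of 0.70 to 0.80, the AUPRC change at HR 1.2 is 15% to 17% and the Brier change is 17%.

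**3. Population effect on the metrics that do not depend on prevalence**

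Suppose the pooled model discriminates less well in PWH: AUC 0.75 in PWoH and 0.65 in PWH (assumed), HR 1.20, the same score distribution in all non-cases, and one cut-off of 0.5 on the score scale.

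- Pooled AUC: 0.893 × 0.75 + 0.107 × 0.65 = 0.739, against 0.65 in PWH.
- Sensitivity: 0.675 in PWoH and 0.518 in PWH. Specificity: Φ(0.5) = 0.691.
- Pooled sensitivity: 0.893 × 0.675 + 0.107 × 0.518 = 0.658. Balanced accuracy: (0.658 + 0.691)/2 = 0.675 pooled, against (0.518 + 0.691)/2 = 0.605 in PWH.

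The pooled figures barely register the weaker performance in PWH, on the primary metric as on the AUC.

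**4. Precision of a shared PWH test set**

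With 2 600 PWH and 34 to 40 events, the standard error of one balanced accuracy (sensitivity = specificity = 0.70) is ½√(0.21/events + 0.21/non-events) = 0.040 to 0.037. The Hanley–McNeil standard error of an AUC of 0.75 is 0.049 to 0.045.

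**The case against.** - **The comparison has no stated object.** The substudy sentence could mean Cox against ML within PWH. That reading is possible, but the same sentence refers to the previous models, so a comparison with them is the plainer one. The different test populations are inferred from the text, not stated in it.
- **The deciding metric does not depend on prevalence.** This is correct. A reader might infer that the whole comparison is driven by event rates. The documents do not support that: balanced accuracy is weighted most, and neither it (at a fixed cut-off) nor the concordance index or time-dependent AUC moves with prevalence as such. They are affected by who is scored (step 3), not by how common CRC is.
- **Matching limits case mix.** It does so for age, sex, region of birth and the named comorbidities. It does not make predictors act equally in PWH and PWoH.
- **The purpose is not stated.** A reader might infer that the substudy is meant to justify adding PWoH. No section says so. It is called exploratory and also differs in modelling approach, so even a shared test set would not isolate the effect of adding PWoH unless models of the same type are compared.
- **Leakage.** A reader might infer that test-set PWH in the substudy will already have trained the pooled model. That would need a fresh split, which the article does not describe.
- **A condensed article leaves detail to the full plan.** This is fair for split indices and interval methods. But the article itself commits to the comparison, and its general promise of subgroup analyses names no scoring of the pooled models in PWH.

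**Conclusion.** The point holds as a defect in how the comparison is fixed. On the plain reading, the pooled figures come from a test set that is about 91% PWoH, with about 89% of its events in PWoH at HR 1.20, and the substudy figures come from PWH alone. A difference between them cannot be interpreted, on the primary metric or on any other.

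The prevalence effect is an additional problem confined to AUPRC and Brier. It is modest at the protocol's own HR (about 16% and 17%), absent at HR 1.0, and large only at HRs that are my assumption. The two metrics also move in opposite senses, so the PWH-only model would look better on one and worse on the other with no real difference in discrimination.

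These sizes rest on an assumed AUC, a binormal score, calibrated models and 10-year risks taken as rate × time. The AUC gap in step 3 is an illustration, not a prediction. The composition of the test set depends only on the 1:10 ratio, provided the time-based split preserves it.

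**What to change.** Amend the substudy section, with a matching line under Stacking and dissemination, to say:

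1. One partition of the PWH is fixed before modelling and used in both analyses.
2. The pooled and PWH-only models are scored on the same held-out PWH, none of whom trained either model.
3. Models of the same type are compared (Cox with Cox, ensemble with ensemble), and paired differences are reported with bootstrap intervals.
4. Metrics taken from different test populations are not compared.

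The cost is wording and shared split indices, with no new data. The drawback is precision: with about 34 to 40 events (HR 1.0 to 1.2, 10 years, 20% split) the intervals will be wide, and the protocol should say so. Pairing recovers some precision, because both models are scored on the same people.

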#### Sensitivity analysis—incomplete data

A sensitivity analysis, using ML techniques that handle missing data natively, will be conducted with PWH only, and the results will be compared with the substudy results to compare the handling of missing data.

The unsupervised analysis for the incomplete data will consist of principal component analysis and t-distributed stochastic neighbour embedding methods to perform dimensionality reduction. The supervised analysis for the incomplete data will use XGBoost models, decision trees and random forests. All these methods can handle missing values natively and therefore will be implemented for the sensitivity analysis.

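### The incomplete-data sensitivity analysis wrongly treats standard PCA and t-SNE as handling missing values natively, and does not commit to the same learners as the substudy it is compared with

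*Protocol article*

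**What the plan says.** Under *Data preparation*, the Protocol article sets a complete-case rule for the study. Variables with more than 10% missing are left out, and then any record that is still incomplete is dropped. The reason given is that little is missing.

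The section *Sensitivity analysis—incomplete data* describes the check on that rule: "A sensitivity analysis, using ML techniques that handle missing data natively, will be conducted with PWH only". It has two arms.

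- Unsupervised: "The unsupervised analysis for the incomplete data will consist of principal component analysis and t-distributed stochastic neighbour embedding methods".
- Supervised: "The supervised analysis for the incomplete data will use XGBoost models, decision trees and random forests".

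The section then gives its reason for the choice: "All these methods can handle missing values natively and therefore will be implemented for the sensitivity analysis". Its purpose is also explicit: "the results will be compared with the substudy results to compare the handling of missing data".

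The comparator is in *Substudy—PWH only*: "A simple Cox PH regression model will be developed using preselected covariates using existing knowledge of risk factors". Beyond that model, the substudy is exploratory, "implementing ML methods to handle overfitting and class imbalance as needed", with no learner named. Performance there is to be judged in the same way as for the main models.

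**The concern.** There are two problems, of different strength.

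The first is a statement of fact that is wrong for two of the methods it covers. Standard PCA decomposes a complete data or covariance matrix. Standard t-SNE starts from the distances between all pairs of people. Neither has a rule for an empty cell. An analyst who follows the section will either get an error or have to choose a workaround after seeing the data. One workaround is to drop the incomplete records, which would bring back the very restriction that the analysis is meant to relax.

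The second is what the comparison can be relied on to show. If the two sides differ in learner as well as in data handling, a gap in performance has two possible sources. The absence of a gap is no clearer, because the two effects may offset each other.

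This is the only missing-data check that the article describes, so it is what a reader would turn to when asking whether the complete-case rule affected the prediction model for PWH.

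**Working it through.** **Step 1: do PCA and t-SNE accept missing cells?** The article gives no figure to reproduce, so the property itself was tested. A 200 × 5 matrix of simulated normal values had one cell set to missing.

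- *PCA, covariance route.* Every covariance that involves the affected variable is undefined: one row and one column of the 5 × 5 matrix, 5 + 5 − 1 = 9 of 25 entries. The run gave 9 of 25.
- *PCA, singular value decomposition route.* The decomposition did not converge.
- *t-SNE input.* Every distance from the affected person to the other 199 is undefined. The run gave 199 undefined distances, out of 200 × 199 / 2 = 19,900.
- *Library routines.* The PCA and t-SNE routines in scikit-learn 1.9.0 both stopped, reporting that they do not accept missing values natively. *Data analysis plan* names Python as one of the two tools; it does not name this library.

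The statement is thus wrong for 2 of the 5 named methods, which form the whole unsupervised arm. XGBoost does handle missing values natively. Decision trees and random forests do so in some implementations.

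**Step 2: does another reading rescue the sentence?** Suppose it refers only to the supervised methods named just before it. The opening sentence of the section still describes the analysis as one that uses natively capable techniques, and PCA and t-SNE are still assigned to the incomplete data. No section names an imputation step or a missing-data variant of either method.

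**Step 3: what changes between the two sides of the comparison?**

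| Element | Substudy, PWH only | Sensitivity analysis, PWH only |
|---|---|---|
| Missing data | Complete cases, under the study-wide rule | Incomplete records kept |
| Named supervised model | Simple Cox model, preselected covariates | XGBoost, decision trees, random forests |
| Other supervised models | Machine learning as needed, not named | None |
| Unsupervised step | None named | PCA and t-SNE |

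The one model that the substudy names is absent from the sensitivity analysis. None of the three supervised learners in the sensitivity analysis is named in the substudy. The stated purpose needs the first row to change while the learner stays the same; the text does not secure that.

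**Step 4: how much could the complete-case rule matter?** The article gives no missingness by variable, so this is an illustration under an assumption: 10 variables, each missing independently in a share *m* of people. The share with complete records is (1 − *m*)^10, applied to the article's 13,000 PWH.

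- *m* = 2%: 0.98^10 = 0.817, about 10,600 people kept.
- *m* = 5%: 0.95^10 = 0.599, about 7,800 kept.
- *m* = 10%, the most that the rule allows: 0.90^10 = 0.349, about 4,500 kept.

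Low missingness in each variable does not by itself ensure a small loss of people. These figures say nothing about the actual loss in this study.

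**The case against.** The strongest reply concerns the comparison. The substudy is not limited to Cox regression, and its machine-learning part is open. The learners named in the sensitivity analysis largely repeat the families used in the main ensemble (XGBoost, Random Survival Forests, decision trees). If the substudy reuses them on complete cases, a like-for-like comparison exists. An article may also leave the list of substudy learners to a fuller plan, and the pipeline figure is not available here. This stands. A reader might infer that the comparison cannot show the effect of complete-case analysis at all, but the text supports only that it does not commit to the same learners.

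Three further replies also stand.

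- A reader might infer that half of the analysis cannot run. The supervised arm is not said to depend on PCA or t-SNE, so the comparison of predictions can go ahead even if the unsupervised arm fails.
- A reader might object that standard t-SNE cannot place new people in its map and so cannot be used on a test set. The article plans "principal component analysis and t-distributed stochastic neighbour embedding methods to perform dimensionality reduction" and does not say that the output feeds a prediction model or is applied to held-out people. A descriptive map needs no such step. The rule on adding variables to both training and test sets concerns cluster labels from the main analysis.
- A reader might conclude that multiple imputation is required. Native handling in tree-based learners is a legitimate choice for a prediction model.

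Two replies carry less weight. The software test covers one library's default routines, but the covariance and distance calculations fail without that library too. Variants of PCA that estimate missing cells do exist, but each brings its own missing-data model and the article names none. Finally, the article says that missing data are minimal. That may limit the practical effect, but it does not make the sentence about the methods correct.

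**Conclusion.** The point holds in two parts.

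The claim of native handling is wrong for standard PCA and t-SNE. As described, the unsupervised arm cannot be run on incomplete data without an unstated imputation step or variant, or a return to complete cases. This part is firm. It rests only on the standard form of the two algorithms being meant, and nothing in the article points to another form.

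The comparison with the substudy does not commit to the same learners, so a performance difference may mix missing-data handling with a change of method. This part is conditional: it falls away if the substudy fits XGBoost, trees and forests to complete cases, which the article neither promises nor rules out.

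The size is moderate. This is a secondary analysis in PWH only, and the main model does not depend on it. No effect on predictive performance can be calculated, because the article gives no missingness figures. It is worth correcting because it is the only missing-data check described and the repair is cheap.

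**What to change.** Rewrite the paragraph on the incomplete-data sensitivity analysis so that it does three things.

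1. Limit the statement about native handling to methods and implementations for which it is true.
2. Drop PCA and t-SNE from this analysis. If they are kept, name a version that copes with missing cells, such as probabilistic PCA, or an imputation step fitted within the training folds.
3. State that the same learners, with the same folds and metrics, will be fitted to the complete-case and to the incomplete PWH data, and that both versions will be evaluated on the same held-out PWH.

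Multiple imputation of the substudy's Cox model, with the same covariates, would be a useful addition but is optional.

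The cost is one reworded paragraph and some computing time. No new data are needed, and the main analysis does not change.
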